**Methods:**

A total of 300 subjects aged between 18 and 40 years which prepared for HT cycle FET will be enrolled in the study. The patients were from five different hospitals, with 60 patients from each hospital. Patients were randomly divided into two groups, and medication was started on the day of endometrial transformation. After FET 28 days, B-ultrasound was done to determine whether to continue the medication. Baseline assessments were carried out before the trial and outcomes were collected 4, 6, 8, 10, and 12 weeks of each gestational cycle.

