### Aims

#### The primary objective and secondary objectives

The primary aim of this trial is to evaluate and verify the clinical efficacy of GSATP, and its effect on the ongoing pregnancy rate (OPR) of HT FET cycles. The secondary objectives are to determine whether GSATP affects implantation rate (IR), clinical pregnancy rate (CPR), and threatened abortion rate (TAR) of HT cycle FETs.

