## Methods

### Diagnostic criteria

The GSATP is suitable for early threatened abortion (TA), which belongs to kidney yin deficiency in TCM. Early TA refers to the premonitory abortion within 12 weeks of pregnancy, which is mainly characterized by a small amount of vaginal bleeding, paroxysmal lower abdominal pain or low back pain, unopened cervical opening, undamaged fetal membrane, and the size of the uterus is consistent with the gestational week [19]. Kidney yin deficiency syndrome in TCM can be diagnosed as long as the waist and knees are sour and soft and any other one of the following symptoms: falling pain in the lower abdomen, or accompanied by dizziness and tinnitus, dry mouth and dry throat, mental fatigue, and feverish palms and soles.

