### Interventions

A randomized, double-blind control method was used to select eligible patients according to the ratio of 1:1 between GSATP and placebo. The GSATP (Product specification: 6 g* 9 bags) and placebo (starch as an ingredient, without the active ingredients) were obtained from Beijing bran Pharmaceutical Inc and re-labeled by Beijing bran Pharmaceutical Inc, according to the national drug standards of the State Food and Drug Administration of China. In this paper, the application research of GSATP in the treatment of threatened abortion is consistent with the indications in its published instructions.

The routine dose of GSATP (6 g tid) or placebo (6 g tid) was orally administered to patients four hours before the endometrial transformation. We ask patients to take their medicine on time every day. Clinical pregnancy was confirmed by interpreting B-ultrasound results 28 days after FET. Oral administration of the treatment on pregnant women was continued until 12 weeks of pregnancy, but drug administration was not done on patients who had not conceived. Patients with ectopic pregnancy were included in adverse events. Both doctors and patients were blinded to the identity of the syringe contents. Patients were allowed to use other drugs in case of emergency, but data from such patients were not included in the statistical analysis.

Adherence reminder sessions were done during the initial product dispensing and at each follow-up visit. The following was communicated to the patients beforehand: the importance of adhering to the daily study product instructions, including the time taken, the importance of storing the study drug appropriately and making the entire study drug, and the measures to be taken in case of missed doses. One of our staff regularly contacted the patients via WeChat to enquire about the medication.

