### Outcome measures

The primary endpoint was OPR at week 12 of pregnancy. The secondary endpoints were IR, CPR, and TAR. The OPR, IR, CPR, and TAR were measured at the end of the experiment. Hormone levels were monitored and recorded at FET on days 1, 7, and 14. IR (%) = number of implantation gestational sac/number of transferred embryo × 100%, CPR(%) = number of clinical pregnancy/number of transfer cycle × 100%, OPR(%) = number of continuous pregnancy/number of transfer cycle × 100%, and TAR(%) = number of abortion/number of clinical pregnancy × 100% (Table 1).

**Table 1 Tab1:** Checklist of items for reporting trials of Chinese herbal medicine formulas

Section/topic	Item number	Standard CONSORT checklist item	Extension for CHM formulas	Reported on page number
**Title, abstract, and keywords**	1a	Identification as a randomized trial in the title	Statement of whether the trial targets a TCM pattern, a Western medicine-defined disease, or a Western medicine-defined disease with a specific TCM pattern, if applicable	1–4;19–49;52
	1b	Structured summary of trial design, methods, results, and conclusions (for specific guidance, see CONSORT for abstracts [26, 27])	Illustration of the name and form of the formula used, and the TCM pattern applied, if applicable	39–45;86–94
	1c		Determination of appropriate keywords, including “Chinese herbal medicine formula” and “randomized controlled trial”	52

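### The secondary outcome called threatened abortion rate has a formula that, read literally, gives an early pregnancy loss rate, and its denominator is selected after treatment has begun

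*Protocol article*

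**What the plan says.** The Aims section of the protocol article lists, among the secondary objectives, whether the pill affects the "threatened abortion rate (TAR) of HT cycle FETs". The abstract's Discussion says that the difference in this rate between the two groups will be analysed statistically.

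The Diagnostic criteria section says what threatened abortion is: "Early TA refers to the premonitory abortion within 12 weeks of pregnancy". It describes slight bleeding or pain, and adds the signs that the pregnancy is still in place: "unopened cervical opening, undamaged fetal membrane, and the size of the uterus is consistent with the gestational week".

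The Outcome measures section then gives the formula: "TAR(%) = number of abortion/number of clinical pregnancy", as a percentage. The clinical pregnancy rate (CPR) and OPR formulas in the same section use transfer cycles as the denominator.

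On timing, the abstract's Methods say that "medication was started on the day of endometrial transformation". The Interventions section says that "Clinical pregnancy was confirmed by interpreting B-ultrasound results 28 days after FET".

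**The concern.** There are two separate difficulties.

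The first is that name and formula do not match. Under the protocol's own description, a woman with threatened abortion has a continuing pregnancy. If she stays pregnant, a formula that counts abortions gives her no event. A woman who loses the pregnancy without any warning sign does count. The rate would then say little about threatened abortion, which is the condition that the Diagnostic criteria and Interventions sections give as the pill's use. A significant difference in either direction could be misread as evidence on that use.

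The second is the denominator. Clinical pregnancy is established on treatment, and the Aims section asks whether treatment changes it. The women who enter the ratio may therefore differ between arms in ways that randomisation does not balance.

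**Working it through.** **Step 1: the definitions side by side.** The documents state no expected TAR, effect size or power, so there is no figure to reproduce.

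| | Diagnostic criteria | TAR formula, read literally |
|---|---|---|
| Event | Warning signs, pregnancy intact | Abortion |
| Warning signs, pregnancy continues | Counted | Not counted |
| Loss without warning signs | Not counted | Counted |

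No section says that abortion in the formula stands for threatened abortion.

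**Step 2: what the literal ratio adds.** Let T be transfer cycles, P clinical pregnancies, A abortions and G ongoing pregnancies. Then CPR = P/T, TAR = A/P and OPR = G/T. If every clinical pregnancy is either ongoing or counted as an abortion, G = P − A, so

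CPR × (1 − TAR) = (P − A)/T = OPR, or TAR = 1 − OPR/CPR.

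For example, an assumed CPR of 0.70 and OPR of 0.60 give 1 − 0.60/0.70 = 14.3%. If x clinical pregnancies are ectopic or lost to follow-up, the left side exceeds OPR by x/T. The identity is therefore approximate in practice.

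**Step 3: when the denominator is fixed.** Treatment starts around endometrial transformation, and clinical pregnancy is confirmed 28 days after transfer. Membership of the denominator is thus a post-randomisation outcome, observed on treatment.

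**Step 4: what this can do.** All rates here are assumed. Take 150 women per arm with one transfer each. Placebo has c pregnancies with loss risk l. Treatment leaves those unchanged and adds e pregnancies with loss risk m. Then

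TAR on treatment = (c·l + e·m)/(c + e), which exceeds l only if m > l.

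*Example A:* c = 75, l = 20%, e = 15, m = 50%.
- Placebo: 15/75 = 20%; OPR (75 − 15)/150 = 40%.
- Treatment: (15 + 7.5)/90 = 25%; OPR (90 − 22.5)/150 = 45%.

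*Example B:* c = 75, l = 15%, e = 15.
- Placebo: 11.25/75 = 15.0%; OPR 63.75/150 = 42.5%.
- Treatment, m = 30%: 15.75/90 = 17.5%; OPR 74.25/150 = 49.5%.
- Treatment, m = 50%: 18.75/90 = 20.8%; OPR 71.25/150 = 47.5%.

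In each case the ratio looks worse although no existing pregnancy was harmed. With m below l it would look better instead.

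**Step 5: does a denominator of all randomised women cure this?** Using Example A, losses per woman randomised are 15/150 = 10% and 22.5/150 = 15%. The apparent worsening is again 5 points, with pooled z = 0.05/√(0.125 × 0.875 × 2/150) ≈ 1.3. Per clinical pregnancy, z = 0.05/√(0.227 × 0.773 × (1/75 + 1/90)) ≈ 0.8. The wider denominator restores the randomised comparison, but a loss count still rises when more women conceive.

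**Step 6: how many women the ratio rests on.** At an assumed CPR of 50% to 60%, 150 per arm gives 75 to 90 women. The 130 per arm that the Sample size section gives before its allowance for loss gives 65 to 78.

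**The case against.** The best defence is that abortion in the formula is shorthand. The Diagnostic criteria themselves describe threatened abortion as a kind of premonitory abortion, the formula stands under the TAR label, and the Allocation concealment section even prints the abbreviation as TAE. The wording is loose throughout, so the authors may have meant to count threatened abortions. This cannot be excluded. On that reading, the mismatch in Step 1 and the identity in Step 2 fall away. The formula would still have to say which event is counted, because sites could otherwise count different ones, and the denominator would still be selected after randomisation.

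It is also fair to say that the bias examples are assumed, that their direction follows from the assumptions, and that TAR is one of three secondary endpoints. CPR and OPR are reported beside it, so a careful reader could see whether a higher ratio merely accompanies more pregnancies. These points stand, and they limit the weight of the finding.

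A reader might infer that the trial compares non-randomised groups. It does not: all women are randomised 1:1. What is compared on TAR is a subset of each randomised arm, selected on a later outcome.

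**Conclusion.** As written, the outcome's name and the protocol's own definition do not agree with the formula, and no other section reconciles them. Read literally, the formula does not answer the stated secondary objective. Under either reading, a between-arm test of a rate per clinical pregnancy is not protected by randomisation.

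The finding has limits. A reader might conclude that the numerator is certainly completed miscarriages, but the text says only abortion. A reader might conclude that TAR is wholly redundant, but that needs the literal reading, complete follow-up and no ectopic pregnancies; the Sample size section expects 10% loss, and the Interventions section foresees ectopic pregnancies. A reader might also conclude that the ratio will make the pill look harmful, but the documents give no rates from which direction or size could be derived; the gaps of 2.5 to 5.8 points in Step 4 are illustrations only.

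The primary endpoint, OPR at week 12, and its sample size are untouched. This should be corrected before analysis, but it does not threaten the main result.

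**What to change.** 1. Rename the printed ratio *early pregnancy loss per clinical pregnancy*. Report it descriptively beside CPR and OPR per transfer cycle, and do not present it as evidence on threatened abortion.
2. Define TAR separately as the occurrence of threatened abortion by the protocol's own Diagnostic criteria, recorded up to week 12 of pregnancy at the visits already planned. If this was the intended meaning all along, say so and correct the numerator.
3. If losses or threatened abortions are also counted per woman randomised, state that they must be read beside OPR, because they can rise simply when more women conceive. Rest efficacy conclusions on OPR.

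The cost is small: two outcome definitions and a few added form items. It is slightly more than wording, because the Safety assessment section records reactions, adverse events and medication-related symptoms without expressly listing the signs of threatened abortion. The investigators should confirm that the signs needing an examination can be recorded at those visits. Sample size and primary analysis do not change.

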**Introduction**				
**Background and objectives**	2a	Scientific background and explanation of rationale	Statement with biomedical science approaches and/or TCM approaches	55–95
	2b	Specific objectives or hypotheses	Statement of whether the formula targets a Western medicine–defined disease, a TCM Pattern, or a Western medicine-defined disease with a specific TCM Pattern	96–99;106–111
**Methods**				
Trial design	3a	Description of trial design (such as parallel, factorial), including allocation ratio		156–161
	3b	Important changes to methods after trial commencement (such as eligibility criteria), with reasons		Not applicable
Participants	4a	Eligibility criteria for participants	Statement of whether participants with a specific TCM Pattern were recruited, in terms of (1) diagnostic criteria and (2) inclusion and exclusion criteria. All criteria used should be universally recognized, or reference given to where detailed explanation can be found.	113–122; 137–144
	4b	Settings and locations where the data were collected		124–128
Interventions	5	The interventions for each group with sufficient details to allow replication, including how and when they were actually administered	Description(s) for different types of formulas should include the following: 5a. **For fixed CHM formulas** 1. Name, source, and dosage form (e.g., decoctions, granules, powders) 2. Name, source, processing method, and dosage of each medical substance. Names of substances should be presented in at least 2 languages: Chinese (Pinyin), Latin, or English. Names of the parts of the substances used should be specified. 3. Authentication method of each ingredient and how, when, where, and by whom it was conducted; statement of whether any voucher specimen was retained, and if so, where they were kept and whether they are accessible 4. Principles, rationale, and interpretation of forming the formula 5. Reference(s) as to the efficacy of the formula, if any 6. Pharmacologic study results of the formula, if any 7. Production method of the formula, if any 8. Quality control of each ingredient and of the product of the formula, if any. This would include any quantitative and/or qualitative testing method(s); when, where, how, and by whom these tests were conducted; whether the original data and samples were kept, and, if so, whether they are accessible. 9. Safety assessment of the formula, including tests for heavy metals and toxic elements, pesticide residues, microbial limit, and acute/chronic toxicity, if any. If yes, it should be stated when, where, how, and by whom these tests were conducted; if the original data and samples were kept; and, if so, whether they are accessible. 10. Dosage of the formula, and how the dosage was determined 11. Administration route (e.g., oral, external) **5b. For individualized CHM formulas** 1. See recommendations 5a 1–11 2. Additional information: how, when, and by whom the formula was modified **5c. For patent proprietary CHM formulas** 156–163 1. Reference to publicly available materials, such as pharmacopeia, for the details about the composition, dosage, efficacy, safety, and quality control of the formula 2. Illustration of the details of the formula, namely (1) the proprietary product name (i.e., brand name), (2) name of manufacturer, (3) lot number, (4) production date and expiry date, (5) name and percentage of added materials, and (6) whether any additional quality control measures were conducted 3. Statement of whether the patent proprietary formula used in the trial is for a condition that is identical to the publicly available reference **5d. Control groups 156–161** Placebo control 1. Name and amount of each ingredient 2. Description of the similarity of placebo with the intervention (e.g., color, smell, taste, appearance, packaging) 3. Quality control and safety assessment, if any 4. Administration route, regimen, and dosage 5. Production information: where, when, how, and by whom the placebo was produced Active control 1. If a CHM formula was used, see recommendations 5a–5c 2. If a chemical drug was used, see item 5 of the CONSORT Statement (24)	86–92; 162–176; 201–202 Since GSATP is a national class III new drug approved according to the new drug registration standard, its specific content is confidential, so it cannot be published. The drug instructions can be queried at the address provided in the article. The rest are not applicable.
Outcomes	6a	Completely defined, prespecified primary and secondary outcome measures, including how and when they were assessed	Illustration of outcome measures with Pattern in detail	187–194
	6b	Any changes to trial outcomes after the trial commenced, with reasons		Not applicable
Sample size	7a	How sample size was determined		196–202
	7b	When applicable, explanation of any interim analyses and stopping guidelines		179–188
Randomization				
Sequence	8a	Method used to generate the random allocation sequence		220
	8b	Type of randomization; details of any restriction (such as blocking and block size)		220–224
Allocation concealment mechanism	9	Mechanism used to implement the random allocation sequence (such as sequentially numbered containers), describing any steps taken to conceal the sequence until interventions were assigned		225–232
Implementation	10	Who generated the random allocation sequence, who enrolled participants, and who assigned participants to interventions		222; 226–232
Blinding	11a	If done, who was blinded after assignment to interventions (for example, participants, care providers, those assessing outcomes) and how		230–233
	11b	If relevant, a description of the similarity of interventions		164–165
Statistical methods	12a	Statistical methods used to compare groups for primary and secondary outcomes		205–212
	12b	Methods for additional analyses, such as subgroup analyses and adjusted analyses		Not applicable
**Results**				
Participant flow (a diagram is strongly recommended)	13a	For each group, the numbers of participants who were randomly assigned, received intended treatment, and were analyzed for the primary outcome		This is only a research protocol, and the subjects have not been recruited, so this item is not applicable.
	13b	For each group, losses and exclusions after randomization, together with reasons		This is only a research protocol, and the subjects have not been recruited, so this item is not applicable.
Recruitment	14a	Dates defining the periods of recruitment and follow-up		135–136; 185–187
	14b	Why the trial ended or was stopped		167–169; 186–188
Baseline data	15	A table showing baseline demographic and clinical characteristics for each group		This is only a research protocol, and the subjects have not been recruited, so this item is not applicable.
Numbers analyzed	16	For each group, number of participants (denominator) included in each analysis and whether the analysis was by original assigned groups		This is only a research protocol, and the subjects have not been recruited, so this item is not applicable.
Outcomes and estimation	17a	For each primary and secondary outcome, results for each group, and the estimated effect size and its precision (such as 95% confidence interval)		This is only a research protocol, and the subjects have not been recruited, so this item is not applicable.
	17b	For binary outcomes, presentation of both absolute and relative effect sizes is recommended		Not applicable.
Ancillary analyses	18	Results of any other analyses performed, including subgroup analyses and adjusted analyses, distinguishing prespecified from exploratory		Not applicable.
Harms	19	All important harms or unintended effects in each group (for specific guidance, see CONSORT for harms [28])	(There is no extension for this item)	Not applicable.
**Discussion**				
Limitations	20	Trial limitations; addressing sources of potential bias; imprecision; and, if relevant, multiplicity of analyses		271–274
Generalizability	21	Generalizability (external validity, applicability) of the trial findings	Discussion of how the formula works on different TCM Patterns or diseases	Not Applicable.
Interpretation	22	Interpretation consistent with results, balancing benefits and harms, and considering other relevant evidence	Interpretation with TCM theory	Not applicable.
**Other information**				
Registration	23	Registration number and name of trial registry		50
Protocol	24	Where the full trial protocol can be accessed, if available		Not applicable.
Funding	25	Sources of funding and other support (such as supply of drugs), role of funders		292–294

*CHM* Chinese herbal medicine, *CONSORT* Consolidated Standards of Reporting Trials, *TCM* traditional Chinese medicine

The original CONSORT items are provided; elaborations for CHM formulas are in italicized text. We strongly recommend reading this checklist in conjunction with the CONSORT 2010 Explanation and Elaboration [29] for important clarifications on all original items of CONSORT Statement

### Statistical analysis

#### Sample size

The sample size was calculated based on a primary study [20], that revealed the rate of ongoing pregnancy in the observation group was significantly higher than that of the control group (63.83% VS 42.86%, *x*^2^=4.24, *P*< 0.05). An estimated OPR of 0.6 was obtained. According to 1:1 ratio, 65% efficacy of GSATP, *α*=0.05 and *β*=0.2, there were 130 patients in the treatment group and 130 in the placebo group. Considering the complexity of clinical practice, the loss rate is estimated to be 0.1. Finally, the sample size was calculated to be 300 subjects.

#### Analysis

The study data were collected and managed by non-clinical staff who were responsible for data management in each clinical center. The data were shown as follows: continuous variables with normal distribution were presented as means±SD, and the count data are presented in the form of n (%). Statistics were run using SPSS version 21 software (SPSS, Inc., Chicago, IL). The differences between the two groups were detected using *χ*^2^ for counting data or t test used for comparative analysis of measuring data. *P* values of less than 0.05 were considered to be statistically significant.

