### Recruitment

We recruited participants who purposed to do FET from reproductive centers in five different tertiary hospitals: Affiliated Hospital of Shandong University of Traditional Chinese Medicine, Maternity and Child Health Care of ZaoZhuang, Shanxi Maternal and Child Health Care Hospital, The First Affiliated Hospital of Wenzhou Medical University, and Jinan Military General Hospital. These five hospitals are all tertiary A public hospitals and have the qualification of IVF-FET, recruiting 60 patients in each hospital. In order to ensure the consistency of the procedures in all the sites, the training was uniformly conducted before the start of the trial. During the trial, all the sites communicated in a timely manner through the network, and the progress was regularly checked by professionals to ensure the consistency and uniformity of the trial. This study was conducted according to the Declaration of Helsinki and approved by the Reproductive Medicine Ethics Committee of the Affiliated Hospital of Shandong University of Traditional Chinese Medicine (approval number 20191109). Written informed consent was obtained from patients before study enrollment. Prospective baseline data of patients were collected, including height, weight, basic endocrine level, and detailed IVF process record. Informed consent was obtained from the patients before any study procedures were done. We estimate that it will take about six months to complete this phase of the test. A study flow chart is displayed in Fig. 1.

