### Allocation concealment mechanism

Participants were randomly assigned to either the control group or the experimental group, at a proportion of 1:1 according to the computer-generated random schedule in R software by an assessor who was blinded to the treatment allocation. Assignment concealment was guaranteed because our experiment identified the subjects from the start of the test. The uncertainty of subjects can fully guarantee the effect of allocation concealment.

Clinical recovery was evaluated by an assessor who was blinded to the treatment allocation. The assessor was comprehensively trained before the study was done. Because of the professionalism of the medical profession, neither the participants nor the staff was assigned blindly and naturally, but the distribution of the participants was not disclosed in subsequent evaluations. Patient-related information such as OPR, CPR, IR, and TAE was collected by personnel who were not directly involved in the experiment. The doctors only collected the information at the end of the trial.

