Modern pharmacological studies have found that Chinese medicine Uncaria and Mulberry Parasitoids have an antihypertensive effect, so they have a good effect on hypertensive disorders of pregnancy [24, 25], which is one of the side effects of HT FETcycle mentioned above. In addition, Chinese dodder seed can promote the secretion of hCG from placenta and promote embryonic development by significantly improve ovarian endocrine function [26]. It is clinically found that some people will have symptoms of constipation during pregnancy, and some components of GSATP can alleviate constipation [27]. Therefore, we will also follow up the remission of constipation during the experiment.

This study is a multi-center double-blind clinical trial with some limitations. The trial will not completely rule out clinical treatment bias. It will be difficult to guarantee that patients have similar backgrounds when comparing the two groups. In addition, the 12-week follow-up period completed in this study was limited and longer follow-ups are needed later to provide more reliable results.

In conclusion, the results of this study are expected to provide high-quality methodological evidence for the effectiveness and safety of GSATP adjuvant treatment of HT FET cycles.

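### The only test named for the primary endpoint is an unadjusted chi-square; adjusting for hospital and baseline data already recorded would gain a little precision at almost no cost

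*Protocol article*

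**What the plan says.** All references are to the protocol article.

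- **Endpoint** (Outcome measures): "The primary endpoint was OPR at week 12 of pregnancy". It is a proportion, so it counts as count data.
- **Test** (Analysis): chi-square "for counting data or t test used for comparative analysis of measuring data", judged at P below 0.05. No hospital term, stratification or covariate is named.
- **Checklist** (Table 1): item 12b, "Methods for additional analyses, such as subgroup analyses and adjusted analyses", is marked as not applicable. Item 18, the matching results item, has the same entry.
- **Centres** (Recruitment): five hospitals, "recruiting 60 patients in each hospital".
- **Baseline data** (Recruitment): "Prospective baseline data of patients were collected, including height, weight, basic endocrine level, and detailed IVF process record". Age, BMI and the history of transfers, abortions and implantation failures must also be known to apply the Inclusion and Exclusion criteria.
- **Randomisation** (Allocation concealment mechanism): "at a proportion of 1:1 according to the computer-generated random schedule in R software". Whether the schedule is stratified by hospital is not said.
- **Comparability** (Discussion): "It will be difficult to guarantee that patients have similar backgrounds when comparing the two groups".

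**The concern.** The article names a comparability problem, collects the data that would address it, and then states an analysis that uses none of them. Success rates can differ between IVF units and with a woman's age and history. A test that ignores such factors leaves their variation in the error term. If allocation happens to be balanced within hospital, the crude test also overstates its own standard error.

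Precision is at stake, and so is credibility. If the arms turn out to differ at baseline, an adjustment chosen after unblinding would look driven by the data. One named in advance would not.

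**Working it through.** **1. The plan's own figure.** Inputs from Sample size: OPR 0.60, control rate 0.4286, α = 0.05 (taken as two-sided), β = 0.2. With unpooled variance:

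n per arm = (1.96 + 0.8416)² × (0.60 × 0.40 + 0.4286 × 0.5714) / (0.60 − 0.4286)² = 7.849 × 0.4849 / 0.02938 = 129.6, so 130.

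This reproduces the stated 130 per arm. It is itself an unadjusted calculation, with power of about 80%.

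**2. Is the crude test valid?** I compared Pearson chi-square with an uncorrected Cochran-Mantel-Haenszel (CMH) test by hospital in 40,000 simulated trials per setting. Each had five hospitals with 60 × 0.9 = 54 evaluable women and a true difference of 0.60 − 0.4286 = 17.14 points. The documents give no OPR by hospital, so every spread is an assumption.

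- Simple 1:1 list: the crude test's type I error was about 5% at every spread. A second set of runs, with 52 women per hospital and a constant odds ratio, gave 5.1-5.3%.
- Allocation balanced within hospital: the crude test's size fell to about 4.0% (hospital OPRs 35-67%) and 3.6% (30-72%).

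**3. How uneven could hospitals be under a simple list?** For Binomial(60, 0.5), the chance of a 24:36 split or worse is 0.155. For at least one of five hospitals it is 1 − (1 − 0.155)⁵ = 0.57. This is ordinary sampling variation, which the crude test already allows for.

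**4. Power from stratifying by hospital** (simple list, 17.14 points):

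| Hospital OPRs (assumed) | Crude chi-square | CMH by hospital |
|---|---|---|
| no difference | 80.2% | 79.9% |
| 46-57% | 80.9% | 80.6% |
| 43-59% | 80.7% | 80.9% |
| 35-67% | 80.7% | 82.5% |
| 30-72% | about 81% | about 84% |

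With allocation balanced within hospital, the gains in the last two rows are about 3 and 4 points. The second set of runs, at the odds ratio implied by 63.83% v 42.86%, shows the same pattern (crude v CMH):

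- no spread: 93.2% v 92.4%
- control rates ±10 points across hospitals: 92.1% v 91.7%
- ±20 points: 88.6% v 89.9%
- ±30 points, an extreme case: 80.3% v 86.4%

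A continuity-corrected CMH would undo the gain: at 35-67% it gave about 78-79%, below the crude test.

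**5. Power from baseline covariates.** If covariates explain a share R² of outcome variance, the standard error shrinks by √(1 − R²). The documents give no R²; 5-10% is assumed. Start from 1.96 + 0.8416 = 2.8016, which is 80% power:

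- R² = 0.05: 2.8016 / √0.95 = 2.874; 2.874 − 1.96 = 0.914, power 82%.
- R² = 0.10: 2.8016 / √0.90 = 2.953; 2.953 − 1.96 = 0.993, power 84%.

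The gains in steps 4 and 5 should not simply be added, since hospital and patient mix may overlap.

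**The case against.** The strongest reply is that this is a preference between two valid tests. The gain depends on hospital differences and an R² that the documents do not supply, and it vanishes when hospitals are alike. An article may also leave stratification and covariates to a full protocol or SAP that is not shown. The first part stands in full and limits the point to efficiency. The second part does not remove the point, because the article does state a method for the primary comparison, and a better one is available from data in hand.

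Some stronger readings are tempting but unsupported:

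- **That the crude test is biased or invalid.** Under 1:1 randomisation chance imbalance is noise, and the type I error holds at about 5%.
- **That the list is unstratified.** The article does not say. A quota of 60 per hospital is compatible with separate lists.
- **That the authors expect imbalance.** The Discussion says only that similarity is difficult to guarantee, as a general limitation.
- **That item 12b is a deliberate ruling-out.** The checklist is a weak guide to design: item 19 (harms) has the same entry, although Safety assessment says all adverse events will be recorded.
- **That 80% is the most power the trial can have.** At 63.83% v 42.86% with 130 per arm, 0.2097 / √[(0.6383 × 0.3617 + 0.4286 × 0.5714) / 130] = 3.47, and 3.47 − 1.96 = 1.51, which is about 93%. The 80% belongs to 0.60 v 0.4286.

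**Conclusion.** The point holds as an inexpensive improvement in precision; no validity error is shown. The stated primary test uses neither hospital nor any baseline variable, although both are on record.

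Stratifying by hospital is worth about 0 points of power if hospital OPRs span no more than 43-59%, 2-3 points at 35-67%, and 3-4 points at 30-72%. Covariates with an assumed R² of 5-10% are worth about 2-4 points from a base of about 80%. The conservatism of the crude test (about 3.6-4.0% instead of 5%) applies only if allocation is balanced within hospital and hospitals differ widely. All of these sizes rest on assumed spreads and an assumed R². The facts about the stated method do not.

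**What to change.** Before unblinding, pre-specify one primary analysis of OPR adjusted for hospital and a short fixed list of variables already on record: age, BMI and number of previous implantation failures. A logistic model reported as a standardised risk difference with 95% CI would serve. The simpler option is a CMH test by hospital, stated to be without continuity correction. Keep the crude chi-square as a supportive result, and bring checklist item 12b into line.

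The cost is a few lines of analysis wording and slightly more analysis work, with no extra patient, visit or measurement. The downside is up to about 1 point of power if the hospitals do not differ.
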